### Efficacy outcomes

Comparisons will be performed using two-tailed tests with a statistical significance of 5%. A sensitivity analysis will be carried out based on participants with no resistance to rifampicin, isoniazid, ethambutol, or pyrazinamide. The primary comparison will be performed between the control arm (arm 1) and experimental arm 1 (arm 2). The comparison between the control arm and experimental arm 2 (arm 3) is solely investigational.

#### Analysis of primary outcome

For the primary outcome of this trial, a negative culture conversion rate on liquid media after 2 months of treatment, the culture conversion rate will be estimated as the proportion with a 95% confidence interval for each treatment group. The difference between the control arm and experimental arm 1 (linezolid for 4 weeks) will subsequently be determined using the chi-square test or Fisher’s exact test.

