## Methods/design

### Setting

This randomized controlled trial is to be conducted at four hospitals in South Korea. The flow diagram of the trial is shown in Fig. 1. Three of the hospitals are affiliated with the Seoul National University College of Medicine (Seoul National University Hospital, Seoul National University Bundang Hospital, and Seoul National University Boramae Medical Center), and the other is the National Medical Center in Seoul. All hospitals are located in an urban area.

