### Design

This is a phase II, multicenter, randomized study with three arms. Eligible patients are first screened by safety laboratory testing and using the Xpert MTB/RIF® assay (Cepheid, Sunnyvale, CA, USA) for rifampicin resistance. Patients with TB without resistance to rifampicin are randomized to the following three arms at a 1:1:1 ratio:Arm 1 (control arm): Standard treatment for drug-sensitive pulmonary TB uses isoniazid (6 months), rifampicin (6 months), pyrazinamide (2 months), and ethambutol (2 months) as recommended by the Korean National Guidelines [7] (Table 1).

**Table 1 Tab1:** Dose and schedule of first-line anti-TB drugs recommended by the Korean National Guidelines [7]

Drug	Dosage			Frequency and timing
	Dose/kg	Recommended dose	Maximal dose	
Isoniazid	5 mg/kg	300 mg/day	300 mg/day	Daily, before meal
Rifampicin	10 mg/kg	450 mg (<50 kg)	600 mg/day	Daily, before meal
		600 mg (≥50 kg)		
Pyrazinamide	20–30 mg/kg	1000 mg (<50 kg)		Daily, before or after meal
		1500 mg (50–70 kg)		
		2000 mg (>70 kg)		
Ethambutol	15–20 mg/kg	800 mg (<60 kg)		Daily, before or after meal
		1200 mg (60–80 kg)		
		1600 mg (>80 kg)		Arm 2 (experimental arm 1): Treatment using isoniazid (6 months), rifampicin (6 months), pyrazinamide (2 months), and linezolid is used (600 mg/day, 4 weeks).Arm 3 (experimental arm 2): Treatment using isoniazid (6 months), rifampicin (6 months), pyrazinamide (2 months), and linezolid is used (600 mg/day, 2 weeks).

The study timeline is shown in Table 2. Returned trial product is reconciled at every visit by the research nurse to ensure adherence to the allocated regimen. If a participant misses a scheduled visit, the research nurse makes immediate phone contact. The duty physician makes a decision on discontinuation or modification of the allocated regimen for patients showing clinical deterioration or reporting adverse events associated with the anti-TB treatment. No treatment or intervention is prohibited for the participants, and any ancillary and/or post-trial care is determined by the duty physician.

**Table 2 Tab2:** Study timeline

Visit	Screening	Baseline visit^a^	Treatment							
Visit number	1	2	3	4	5	6	7	8	9	10
Weeks (w)	−2 w to −1 d	0	1 w	2 w	4 w	8 w	12 w	16 w	20 w	24 w
Visit window	NA	NA	±4 d	±4 d	±1 w	±2 w	±2 w	±2 w	±2 w	±2 w
Consent	X									
Randomization		X								
Medical history	X									
Physical examination	X		X	X	X	X	X	X	X	X
Neurologic examination	X		X	X	X	X	X	X	X	X
Xpert MTB/RIF® assay	X									

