### Randomization

We assign participants to study arms using an adaptive stratified sampling method to minimize the imbalance between the numbers of participants in each treatment group over a number of stratification factors: the institution, the presence/absence of cavitation on baseline chest radiographs, and the presence/absence of baseline diabetes mellitus. A centralized web-based system of the Medical Research Collaborating Center of Seoul National University Hospital is used for allocation.

Diabetes mellitus is defined by any one of the following: (1) fasting plasma glucose levels ≥126 mg/dL, (2) random plasma glucose levels ≥200 mg/dL, or (3) the presence of any antidiabetic agent as a concomitant medicine.

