### Stratified analysis

Primary and secondary outcomes will be analyzed separately in participants with sputum smear-positive and smear-negative pulmonary TB.

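### Allocation is balanced on institution, cavitation and diabetes, but the primary test uses none of them, so it is somewhat conservative if these factors predict conversion

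*Protocol article*

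**What the plan says.** Under Randomization, the protocol article assigns participants by an "adaptive stratified sampling method to minimize the imbalance between the numbers of participants in each treatment group". The factors are "the institution, the presence/absence of cavitation on baseline chest radiographs, and the presence/absence of baseline diabetes mellitus". Under Setting there are four hospitals, so institution has four levels, and under Design the ratio is 1:1:1.

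Under Analysis of primary outcome, each arm's conversion rate is "estimated as the proportion with a 95% confidence interval for each treatment group". The difference between the control arm (arm 1) and experimental arm 1 (arm 2, four weeks of linezolid) "will subsequently be determined using the chi-square test" or Fisher's exact test. No covariate or stratum enters that comparison.

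No section of the article uses the three allocation factors in an analysis. The one stratified analysis has outcomes "analyzed separately in participants with sputum smear-positive and smear-negative pulmonary TB", and smear status is not an allocation factor.

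**The concern.** Forcing balance on a factor that predicts the outcome removes part of the chance difference between arms. The ordinary two-by-two variance assumes that this part is still there. The standard error behind the test is then larger than the true sampling variation, and the test rejects too rarely under the null hypothesis. An analysis that includes the factors recovers this precision.

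At stake is a modest amount of efficiency in the one confirmatory comparison. The article names its primary test explicitly, so this is a stated method that does not follow the stated design, not a detail left to another document.

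**Working it through.** **1. The plan's own sample size.** Inputs from the Assumptions section: 75% versus 90%, two-sided α = 0.05, power 85%. With the pooled, uncorrected two-proportion formula:

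n = [1.960·√(2·0.825·0.175) + 1.036·√(0.75·0.25 + 0.90·0.10)]² / 0.15² = (1.0532 + 0.5460)² / 0.0225 = 2.5573 / 0.0225 = 113.7, which rounds up to 114.

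Inflation: 114 / (1 − 0.20) = 142.5, which rounds up to 143. Both stated figures reproduce, and they rest on the unadjusted comparison. Approximate power at 114 per arm is 85.1%. Exact enumeration gives 86.1% for the uncorrected chi-square test.

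**2. Simulation under minimisation.** 4,000 trials per scenario, 342 participants in three arms, minimisation on four sites, cavitation and diabetes (best arm with probability 0.8, otherwise random). Assumed, because the documents give no figures: site shares 40/25/20/15%, cavitation 40%, diabetes 20%, and the odds ratios below. The comparison is arm 2 versus arm 1: unadjusted chi-square against logistic regression on all three factors.

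| Odds ratios (cavitation / diabetes / site) | Type I error, unadjusted | Type I error, adjusted | Power, unadjusted | Power, adjusted | Mean unadjusted SE ÷ actual SD (null; alternative) |
|---|---|---|---|---|---|
| 1 / 1 / 1 | 5.1% | 5.1% | 86.0% | 86.0% | 1.01; 0.99 |
| 2 / 1.5 / 1.3 | 4.8% | 5.2% | 86.6% | 87.2% | 1.01; 1.03 |
| 3 / 2 / 1.5 | 4.6% | 5.6% | 86.5% | 87.9% | 1.04; 1.02 |
| 5 / 3 / 2 | 3.2% | 5.4% | 88.5% | 91.2% | 1.09; 1.10 |

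Monte Carlo standard errors: √(0.05·0.95/4000) = 0.3 points for type I error and √(0.86·0.14/4000) = 0.5 points for power. From the unrounded rates, the power differences are 87.18 − 86.55 = 0.6, 87.90 − 86.45 = 1.5 and 91.15 − 88.45 = 2.7 points.

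**3. Consistency check.** If the standard error is too large by a factor r, the type I error should be 2·[1 − Φ(1.96·r)]. The null-scenario ratios 1.0129, 1.0354 and 1.0915 give 4.7%, 4.2% and 3.2%. The simulated values are 4.8%, 4.6% and 3.2%, so they agree within simulation error.

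**4. A second set-up.** 20,000 trials per scenario with balance within strata of cavitation (40%, odds ratios 0.25-0.5) and diabetes (20%, odds ratios 0.5-0.7), institution left out, analysed by a Cochran-Mantel-Haenszel test.

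- Type I error: unadjusted 4.7 / 4.3 / 4.0%; stratified 5.0 / 4.9 / 5.0%.
- Power: unadjusted 86.1 / 86.8 / 87.2%; stratified 86.4 / 87.7 / 88.6%. The gain is 0.3 to about 1.5 points.

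Here the stratified test held its level, so the gain is not bought with excess type I error.

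**5. Fisher's exact test.** At 114 per arm its exact power is 82.2% and its type I error 3.5%, before any effect of the allocation. Expected non-converters are 114·0.25 + 114·0.10 = 28.5 + 11.4 = 39.9, or about 20 per arm under the null hypothesis. Under the usual small-expected-count convention, that would select chi-square.

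**The case against.** The strongest reply is that little is lost and validity is not threatened. The error is on the conservative side, the loss is nil when the factors are not prognostic, and the unadjusted test matches the sample-size calculation. In every scenario it reached at least 85% power. All of this stands. It is also true that the article gives no prognostic rationale for the three factors, so their strength is an assumption. In addition, the adjusted Wald test ran at 5.2-5.6%, so part of its apparent gain in the minimisation simulation is excess type I error.

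A reader might infer several stronger things that the documents do not support:

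- **That the trial is short of its stated power.** It is not on this ground: 114 per arm reproduces, and chi-square gives 85-86%.
- **That the planned confidence intervals are wrong.** The only intervals stated are for each arm's proportion. No between-arm interval is planned that could be too wide, so the effect falls on the p-value.
- **That the decision on a 4-month trial rests on p alone.** The arm-level rates will be reported with intervals. The abstract's Discussion asks for a higher conversion rate and for safety, and the main Discussion asks for an excellent conversion rate.
- **That naming Fisher's test costs about four power points.** That applies only if Fisher is chosen, which about 20 expected non-converters per arm would not trigger.

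The reply does not remove the mismatch itself: the design uses three factors and the named primary test uses none.

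**Conclusion.** The point holds in a limited form. If institution, cavitation and diabetes predict conversion, the unadjusted test is somewhat conservative: type I error about 4-5% under weak to moderate effects and about 3% under strong effects, with roughly 0.3 to 2.7 power points forgone against an adjusted analysis. The direction is secure whenever the factors are prognostic. The size depends on the assumed prevalences and odds ratios, and the top of the range needs odds ratios as large as 5, 3 and 2. This is a missed efficiency. A significant result from the planned test would remain valid.

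**What to change.** Make the primary comparison of arm 2 with arm 1 adjusted for all three allocation factors. Two suitable forms are:

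- logistic regression on institution, cavitation and diabetes, followed by a standardised risk difference with its 95% confidence interval; or
- a Mantel-Haenszel risk difference and test over strata formed by the three factors, with a rule fixed in advance for pooling sparse strata (4 × 2 × 2 = 16 cells before pooling).

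Institution should be kept in either form, since it is one of the balanced factors. Because the logistic Wald test ran slightly above 5% in the simulation, its type I error should be checked before it is chosen. Keep the unadjusted chi-square test as a sensitivity analysis.

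The cost is a change of wording, made before the outcome data are examined. All three factors are already recorded for allocation, and the sample size need not change.

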#### Analysis of secondary outcomes

The analysis of secondary outcomes will be described as explorative outcomes. The sputum culture conversion rate after 2 months of treatment (solid media) among the three groups will be compared using the chi-square test or Fisher’s exact test. The median time to culture conversion will be calculated in each group and compared using a log-rank test. Cure rate, treatment completion rate, and treatment success rate will be compared among the three groups using the chi-square test or Fisher’s exact test.

### Safety assessment

Grades 1 and 2 peripheral or optic neuropathies and any grade 3 adverse events (AEs), according to the Common Terminology Criteria for Adverse Events, that are considered possibly, probably, or definitely related to the research, and all serious AEs, will be fully and completely documented.

A safety analysis will be performed based on AEs that are identified during the clinical trial. Frequencies and fractions of total AEs, serious AEs, and AEs will be described, together with 95% confidence intervals. In addition, the relatedness of AEs to the trial drug and their seriousness will be summarized. Frequencies of grade 3 or 4 AEs and those of each AE will be compared using the chi-square test or Fisher’s exact test.

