Sputum AFB smear	X	X^d^	X	X	X	X	X	X	X	X
TB culture (solid)	X	X^d^	X	X	X	X	X	X	X	X
TB culture (liquid)	X	X^d^	X	X	X	X	X	X	X	X
DST^b^	With first cultured *Mycobacterium tuberculosis*									
CXR	X	X^d^			X	X	X	X	X	X
HIV, HBV	X									
Total bilirubin, AST/ALT, creatinine	X	X^d^	X	X	X	X	X	X	X	X
Complete blood count	X	X^d^	X	X	X	X	X	X	X	X
Optic test		X	X	X	X	X				
Urine HCG^c^	X									
Compliance of drug intake			X	X	X	X	X	X	X	X
Adverse drug reaction			X	X	X	X	X	X	X	X
Other medications^e^		X	X	X	X	X	X	X	X	X

*w* weeks, *d* days, *NA* not applicable, *AFB* acid-fast bacilli, *TB* tuberculosis, *DST* drug susceptibility test, *CXR* simple chest radiography, *HIV* human immunodeficiency virus, *HBV* hepatitis B virus, *AST* aspartate transaminase, *ALT* alanine transaminase, *HCG* human chorionic gonadotropin

^a^Treatment will be initiated at the baseline visit, as TB treatment should be started promptly following diagnosis

^b^Drug susceptibility test for isoniazid, rifampicin, ethambutol, pyrazinamide, streptomycin, kanamycin, amikacin, capreomycin, ofloxacin, levofloxacin, moxifloxacin, prothionamide, cycloserine, and *para*-aminosalicylic acid

^c^Only in females of childbearing potential

^d^Can be omitted if the results of previous tests within the prior 4 weeks are available

^e^In particular, immunosuppressive agents (including corticosteroids)

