## Discussion

Development of a shorter duration anti-TB treatment regimen could improve not only treatment outcomes of individual patients but also TB control throughout the world. Based on higher culture conversion rates after 2 months of treatment in drug-susceptible TB patients treated with regimens, including moxifloxacin [9, 10], 4-month regimens, including moxifloxacin or gatifloxacin, have been attempted recently. The REMoxTB trial replaced isoniazid or ethambutol with moxifloxacin [11]. The OFLUOTUB trial used gatifloxacin instead of ethambutol [12]. The RIFAQUIN trial included moxifloxacin instead of isoniazid in the intensive phase and used twice-weekly application of moxifloxacin and rifapentine in the continuation phase [13]. Another trial tested three-times-weekly administration of isoniazid, rifampicin, pyrazinamide, and moxifloxacin or gatifloxacin instead of ethambutol [14]. Unfortunately, none of these 4-month treatment regimens showed non-inferiority to a 6-month regimen.

Based on the impressive effectiveness of linezolid in patients with XDR-TB refractory to previous treatment [6], we are performing a trial using linezolid instead of ethambutol for drug-susceptible pulmonary TB. If a new regimen including linezolid shows an excellent culture conversion rate by week 8, which could be a surrogate for relapse [15, 16], it could be tested as a 4-month anti-TB treatment regimen through another clinical trial.

Safety issues of using linezolid for TB treatment will also be addressed through the current trial. Although linezolid is highly effective for the treatment of multidrug-resistant TB, it is frequently accompanied by serious AEs, including peripheral neuropathy and bone marrow suppression. In a recent clinical trial of linezolid in patients with XDR-TB, as many as 87% of patients reported clinically significant AEs [6]. Similarly, a meta-analysis reported AEs in 58.9% of multidrug-resistant or XDR-TB patients who used linezolid [17]. These reports of frequent AEs underscore the limitation of linezolid as a standard drug for treatment of multidrug-resistant TB, which mandates the long-term use of anti-TB drugs. Our trial using linezolid for 2 or 4 weeks, times which are within the permitted duration of use, will reveal the safety of the relatively short-term use of linezolid for patients with TB.

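### The AE documentation rule is narrower than the AE analysis it feeds, so low-grade marrow suppression may be captured only at the investigator's discretion, although blood counts are taken at every treatment visit

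*Protocol article*

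**What the plan says.** All references are to the protocol article.

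- **Documentation rule (Safety assessment, first paragraph).** It covers "Grades 1 and 2 peripheral or optic neuropathies and any grade 3 adverse events (AEs), according to the Common Terminology Criteria for Adverse Events", where these are "possibly, probably, or definitely related to the research, and all serious AEs, will be fully and completely documented". Low grades are named for neuropathy only.
- **Analysis (Safety assessment, second paragraph).** "A safety analysis will be performed based on AEs that are identified during the clinical trial". Frequencies of all AEs and of serious AEs are then to be described with 95% confidence intervals. Grade 3 or 4 AEs, and each individual AE, are to be compared by chi-square or Fisher's exact test. Neither the all-AE summary nor the each-AE comparison has a grade limit. The Abstract also promises that the frequency of all AEs will be documented.
- **Data collected (Design, Table 2).** The row "Complete blood count" is marked at screening, baseline and all eight treatment visits (weeks 1, 2, 4, 8, 12, 16, 20 and 24). For the baseline test, footnote d applies: "Can be omitted if the results of previous tests within the prior 4 weeks are available". The row "Adverse drug reaction" is marked at every treatment visit, with no grade threshold.
- **Harms and purpose (Discussion).** Peripheral neuropathy and bone marrow suppression are named together as linezolid harms, and the trial "will reveal the safety of the relatively short-term use of linezolid for patients with TB". The Abstract makes safety a condition for taking the regimen into a 4-month trial.

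**The concern.** The section lowers the documentation threshold for one of the two harms that the Discussion names and not for the other. The harm left out is the one that a scheduled laboratory test measures in every arm without anyone's judgement. Nothing in the section says when an abnormal count becomes an AE.

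Two consequences follow. First, a site that follows the documentation rule literally need not record a grade 1-2 fall in hemoglobin, neutrophils or platelets, so the all-AE and each-AE analyses would have little of it to count. Second, a site that goes beyond the rule does so knowing the treatment, and may look harder in the linezolid arms. The article itself warns of open-label bias in its closing paragraphs. Either way, the statement about marrow safety would rest on incomplete or unevenly collected events while the blood counts that could settle it are in the database.

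**Working it through.** **1. Capture rule against analysis.** Each type of event is set against the two paragraphs of Safety assessment:

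| Event | Named in documentation rule? | Falls within stated analysis? |
|---|---|---|
| Grade 1-2 peripheral or optic neuropathy | Yes | Yes (all AEs, each AE) |
| Grade 1-2 cytopenia, non-serious | No | Yes, if recorded as an AE |
| Grade 3 cytopenia, judged related | Yes | Yes |
| Grade 3 cytopenia, judged unrelated, non-serious | No | Yes (grade 3 or 4 AEs) |
| Grade 4 cytopenia, non-serious | No, as written | Yes (grade 3 or 4 AEs) |
| Any serious AE | Yes | Yes |

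In three of the six rows the analysis needs events that the rule does not require.

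**2. What discretionary recording does.** Let p be the true proportion with low-grade cytopenia and r the proportion of those cases that are recorded. The observed difference is r_t × p_t − r_c × p_c. If r is the same in both arms, a true difference shrinks by the factor r. If p is the same in both arms, the observed difference is p × (r_t − r_c), which is not zero when recording differs by arm. Grading from the laboratory value sets r to 1 for every count obtained, in every arm.

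**3. The plan's own figure.** For 75% vs 90%, two-sided alpha 0.05 and power 85%, with pooled variance:

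n = [1.96 × √(2 × 0.825 × 0.175) + 1.036 × √(0.75 × 0.25 + 0.90 × 0.10)]² / 0.15² = 113.7, so 114 per arm.

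114 / 0.80 = 142.5, so 143 per arm and 429 in total. Both stated figures reproduce. This point disputes neither, and 143 is used below. The safety group (at least one dose) may be slightly smaller.

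**4. Illustration of size.** The documents give no cytopenia rates, so every rate here is an assumption. Power is for the two-sided Fisher's exact test at 0.05 with 143 per arm:

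| Assumed rates, control vs linezolid | Power |
|---|---|
| Severe only: 0.5% vs 2% | 3.6% |
| Severe only: 1% vs 3% | 8.8% |
| Severe only: 0.5% vs 3% | 15.2% |
| Severe only: 2% vs 5% | 16.9% |
| Severe only: 1% vs 5% | 37.0% |
| Any grade: 10% vs 20% | 60.5% |
| Any grade: 5% vs 15% | 77.3% |
| Any grade: 10% vs 25% | 90.2% |

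A normal approximation gives higher values for the rare events (23% for 1% vs 3%, 51% for 1% vs 5%), but the ordering is the same. At 10% vs 25% the excess is 143 × 0.15 = 21 participants per arm. The 95% confidence interval around 15 points would have half-width 1.96 × √(0.10 × 0.90/143 + 0.25 × 0.75/143) = 8.6 points.

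**5. Counts as continuous values.** With a shift of d standard deviations and baseline correlation ρ, power = Φ(d / √(2(1 − ρ²)/143) − 1.96). For d = 0.3 this is 71.8% at ρ = 0 and 83.4% at ρ = 0.5. For d = 0.4 it is 92.3% and 97.4%. Both d and ρ are assumed.

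**The case against.** A reader might infer that mild to moderate marrow suppression would simply go unreported. The documents do not support that. Safety assessment describes all AEs and compares each AE with no grade limit, the Abstract says that total AEs will be documented, and Table 2 asks about adverse drug reactions at every treatment visit. A grade 1-2 cytopenia that an investigator records as an AE would be counted. The rule about full documentation can also be read as saying which events need full detail, with the rest still tallied, and its mention of grade 3 may have been meant as grade 3 or higher.

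A reader might also treat the absence of a laboratory table as the defect. It is not. A condensed article may leave such tables to the full protocol or analysis plan, which are not shown. Nor do the documents say that the blood counts were scheduled to watch for marrow suppression, or that short linezolid exposure mainly produces moderate falls. The first is an inference and the second an assumption. The monitoring board also sees unblinded data during the trial.

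All of this limits the claim. It does not remove the mismatch. The article states a capture rule, that rule is narrower than the analysis beside it, and no text says when an abnormal count becomes an AE. A later analysis plan based on identified AEs cannot recover cytopenias that were never recorded as AEs. Review by the board does not fix what the final comparison counts.

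**Conclusion.** The point holds as an inconsistency within Safety assessment. The documentation rule is narrower than the planned AE analysis, omits non-serious grade 4 events as written, and gives low-grade marrow suppression no place beside low-grade neuropathy. Capture of low-grade cytopenia is therefore unclear and probably discretionary, not excluded. The safety comparison may miss it or be biased by open-label recording.

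The size cannot be fixed from the documents. Under the assumed rates, the severe-event contrasts have low power (about 4-37%) and the any-grade contrasts moderate to high power (about 61-90%). These figures show that severe events alone carry little information at this sample size. They do not show that an effect on the marrow exists. The sample size and the primary efficacy analysis are unaffected. The change should be made, because it determines what the trial can say about a harm that it names itself.

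**What to change.** 1. In Safety assessment, reconcile the documentation rule with the planned analysis. State which AEs are recorded (by grade, relatedness and seriousness) so that the all-AE, each-AE and grade 3 or 4 summaries have the data they need, and include grade 4 explicitly.
2. Grade every scheduled hemoglobin, neutrophil and platelet result from the laboratory value by the Common Terminology Criteria, in all three arms, with no relatedness filter.
3. Report the worst post-baseline grade by arm as a shift from baseline, using the screening value where the baseline test was omitted under footnote d. Baseline matters because the eligibility criteria admit participants with hemoglobin as low as 7.0 g/dL. Give the between-arm difference in any-grade cytopenia with its 95% confidence interval.
4. Optional and supportive: a baseline-adjusted comparison (ANCOVA) of the counts during the first 8 weeks, reported as mean differences with confidence intervals.

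The cost is a few lines of text and a few more safety tables from data already scheduled. No extra tests, visits or participants are needed, and no treatment or patient-management rule changes.

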**Methods/design:**

This is a phase II, multicenter, randomized study with three arms. We are enrolling patients with pulmonary tuberculosis without rifampicin resistance screened by the Xpert MTB/RIF® assay. The standard treatment arm uses isoniazid (6 months), rifampicin (6 months), pyrazinamide (2 months), and ethambutol (2 months). Experimental arm 1 uses linezolid (600 mg/day) for 4 weeks instead of ethambutol. Experimental arm 2 uses linezolid (600 mg/day) for 2 weeks instead of ethambutol. The primary outcome is the sputum culture conversion rate on liquid media after 2 months of treatment. Secondary outcomes include the sputum culture conversion rate on solid media after 2 months of treatment, time to sputum culture conversion on liquid and solid media, cure rate, and treatment success rate. The frequencies of total adverse events (AEs) and serious AEs will be described and documented. Based on an α = 0.05 level of significance, a power of 85%, a 15% difference in the culture conversion rate after 2 months between the control arm and experimental arm 1 (75% vs. 90%), a 10% default (loss to follow-up) rate, and a 10% culture failure, the required number per arm was calculated to be 143 (429 in total).

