**Discussion:**

This trial will reveal the effectiveness and safety of 2 or 4 weeks of use of linezolid instead of ethambutol for patients with drug-susceptible pulmonary tuberculosis. If a new regimen including linezolid shows a higher culture conversion rate by week 8, and is safe, it could be tested as a 4-month antituberculosis treatment regimen in the future.

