### Statistical analysis

The results of this trial will be analyzed based primarily on the intention-to-treat (ITT) approach. In addition, a per protocol analysis will be performed secondarily. A safety analysis will be performed based on the safety group. The ITT groups will comprise participants who satisfy the inclusion and exclusion criteria, those who are randomized, and those who take the trial drug at least once. The per protocol groups will comprise participants from ITT satisfying the following conditions: (1) participants took the trial drug (ethambutol or linezolid) at greater than 80% of the planned dose (ethambutol, ≥45 days for control arm; linezolid, ≥23 days for experimental arm 1; linezolid, ≥12 days for experimental arm 2), and (2) participants completed the clinical trial according to the protocol. The safety group includes participants who took the trial drug at least once. No interim analysis of the data is planned.

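### The only between-arm safety comparison is a chi-square or Fisher test, so the plan gives no estimate or bound for excess harm over the ethambutol arm

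*Protocol article*

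**What the plan says.** The Safety assessment section describes AEs in two ways. First, estimation: "Frequencies and fractions of total AEs, serious AEs, and AEs will be described, together with 95% confidence intervals". Read plainly, these intervals belong to the frequency or fraction in each arm, and no interval for a difference is mentioned. Second, comparison: "Frequencies of grade 3 or 4 AEs and those of each AE will be compared using the chi-square test or Fisher’s exact test". No other between-arm safety method appears. The safety population is defined under Statistical analysis: "The safety group includes participants who took the trial drug at least once".

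The Methods part of the Abstract is modest about the aim: "The frequencies of total adverse events (AEs) and serious AEs will be described and documented". Two other places ask for more. The Discussion part of the Abstract says that a regimen that "shows a higher culture conversion rate by week 8, and is safe, it could be tested as a 4-month antituberculosis treatment regimen". The main Discussion says that the trial "will reveal the safety of the relatively short-term use of linezolid for patients with TB", just after describing linezolid as often accompanied by serious AEs such as neuropathy and marrow suppression.

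The section Justification of sample size rests on culture conversion alone (75% against 90%). No power or precision is given for any safety outcome.

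**The concern.** The safety question is how much harm linezolid adds when it replaces ethambutol. A test of no difference does not answer it. A small p-value says that some difference exists but not how large it is, and a large p-value does not limit how large it could be. Intervals for each arm limit that arm's own rate but do not directly limit the excess over control.

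The trial was sized for a 15-point difference in conversion, so its tests have little power against small AE differences. A non-significant result would be common even if a real excess of a few points existed. If that result were the main support for a safety statement, a regimen with a relevant excess could meet the second of the two conditions for a further trial.

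**Working it through.** **Inputs from the Protocol article.** 114 evaluable and 143 randomised per arm, 1:1:1 allocation, 75% against 90% conversion, power 85%, two-sided 5%. The two-sided 5% level is stated under Efficacy outcomes, and I assume it also applies to the safety tests.

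**Inputs assumed.** AE rates. The article gives no control-arm rate and no grade 3–4 rate for short-term linezolid. Its figures of 87% and 58.9% come from drug-resistant TB. A range is therefore used.

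**1. The plan's own sample size.** With p̄ = 0.825,

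n = [1.960·√(2·0.825·0.175) + 1.036·√(0.75·0.25 + 0.90·0.10)]² / 0.15² = 113.7, rounded up to 114.

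Allowing 10% + 10%: 114/0.80 = 142.5, rounded up to 143. Both figures are reproduced, and both concern efficacy only.

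**2. Chance that a true excess is non-significant.** For X ~ Bin(143, p_control) and Y ~ Bin(143, p_linezolid), sum P(X = i)·P(Y = j) over all pairs (i, j) that do not give p < 0.05 in the direction of harm.

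| Control vs linezolid | Excess (points) | Missed, chi-square | Missed, Fisher |
|---|---|---|---|
| 1% vs 3% | 2 | 80% | 91% |
| 2% vs 5% | 3 | 74% | 83% |
| 1% vs 5% | 4 | 49% | 63% |
| 2% vs 6% | 4 | 60% | 71% |
| 5% vs 10% | 5 | 65% | 72% |
| 10% vs 15% | 5 | 75% | 80% |
| 5% vs 15% | 10 | 18% | 23% |
| 10% vs 20% | 10 | 33% | 39% |
| 15% vs 25% | 10 | 43% | 49% |
| 20% vs 30% | 10 | 50% | 56% |
| 10% vs 25% | 15 | 7% | 10% |
| 20% vs 35% | 15 | 18% | 22% |

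For excesses of 2 to 5 points the range is 49–91%. For 10 points it is 18–49% at control rates of 5–15%, and a little over half at most when the control rate is 20%. Excesses of 15 points are usually detected.

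**3. What an interval for the difference would add (Newcombe, n = 143 per arm).** With Wilson limits (l, u) for each arm and linezolid as arm A:

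lower = d − √[(p_A − l_A)² + (u_C − p_C)²]; upper = d + √[(u_A − p_A)² + (p_C − l_C)²].

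- 7 vs 1 events: p_A = 0.0490 (0.0239 to 0.0976), p_C = 0.0070 (0.0012 to 0.0385), d = 0.0420. Lower = 0.0420 − √(0.0250² + 0.0316²) = 0.002. Upper = 0.0420 + √(0.0486² + 0.0058²) = 0.091. The excess is +4.2 points (0.2 to 9.1). Fisher gives p = 0.066. The expected count is 4 per arm, so Fisher is the usual choice; uncorrected chi-square would give 0.031.
- 24 vs 14 events: d = +7.0 points, interval −1.0 to +15.0. Fisher p = 0.12, chi-square p = 0.08.
- 0 vs 0 events: the Wilson upper limit is 1.96²/(143 + 1.96²) = 0.026, so the upper limit for the excess is +2.6 points.

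**4. Precision available.** The approximate half-width with equal rates is 1.96·√(2p(1 − p)/143): ±5.1 points at 5%, ±7.0 at 10%, ±9.3 at 20%.

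**The case against.** The case on the other side is substantial. Chi-square and Fisher tests on AE counts are conventional. Phase II trials sized for efficacy are not normally powered for differences of 3 to 5 points, and a formal safety margin is not standard. Safety also does not rest on the test alone. The article plans intervals for AE frequencies, a summary of relatedness and seriousness, repeated blood counts and neurological examinations, and an independent monitoring board that may recommend stopping. An interval for the difference could sit in an analysis plan that is not shown, and a reader can compute one from the reported counts.

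Most of this stands, and it rules out four stronger readings that a reader might infer:

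- That the trial is committed to declaring linezolid safe. The Abstract's sentence is conditional and concerns only a possible later trial, and AE reporting is called descriptive.
- That a non-significant test will be read as safe. No section says so.
- That there is no upper bound at all. The planned intervals do bound each arm's rate: exact upper limits are 2.5% for 0/143 and 9.8% for 7/143. Only a bound on the difference is absent.
- That relevant harms would usually be missed. The table supports this for 2 to 5 points on the assumed rates, but not for 10-point excesses generally and not for 15 points.

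The objection does not remove the core. The between-arm method is stated, not left open, and it is a test that does not measure the excess. Neither the board nor the per-arm intervals supply that estimate for the final report.

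**Conclusion.** The point holds as a minor one. The stated between-arm safety comparison yields no estimate or bound of excess harm against ethambutol, while the article looks to the trial for a safety conclusion. A non-significant result could not by itself support that conclusion, given the miss rates above for excesses of 2 to 5 points and, less strongly, 10 points. These figures rest on assumed AE rates, all 143 per arm in the safety population, a two-sided 5% level, and the plain reading that the planned intervals apply to each arm. The sample size itself is correct, and lack of power for safety is not an error in a phase II trial. What needs changing is the form of the comparison.

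**What to change.** In Safety assessment, replace the sentence on the chi-square or Fisher comparison with wording such as: *For grade 3–4 AEs, serious AEs, peripheral and optic neuropathy, and haematological AEs, the risk difference versus control (arm 2 minus arm 1; arm 3 minus arm 1) will be reported with a 95% confidence interval (for example Newcombe). P-values from chi-square or Fisher tests are descriptive. Any safety statement will refer to the excess that the interval does not exclude; a non-significant test will not be taken as evidence of safety.* Word the safety statements in the Abstract and Discussion to match. No numerical margin is required.

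The cost is a few extra intervals from data already collected, with no added patients or visits. The downside is a less favourable safety statement: even no events in either arm would leave an excess of up to 2.6 points unexcluded.
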